#### Analytic strategy

Aim 1: To use large national datasets to evaluate the effect of a broad range of social drivers and of a social-economic intervention on youth mental health.

In this step we will evaluate: first the effect of the BFP and social drivers such as family income, poverty, early marriage, housing characteristics, family income, parents’ divorce, family composition, and parents’ substance misuse on youth hospitalization from: (A) mood disorders; (B) anxiety; (C) psychosis; (D) prescribed or illicit drug abuse and dependence; (E) alcohol abuse and dependence; (F) alcohol-related liver, problem/chronic liver disease; (G) physical injuries; and (H) attempted suicide and (I) suicide. We will also evaluate if a family history of violence, suicide and psychiatric disorders will be associated with an increased risk of been hospitalized from a mental illness or been a suicide victim among youth. Also, if the BFP reduced the recurrence of mental health-related hospitalizations.

We will run regressions to evaluate the association between important social drivers listed above on mental health-related hospitalizations and suicide among youth in Brazil from 2001 to 2018. Multivariate regression models based on a hierarchical analysis approach will be adjusted for mental health care access, income, location of residence (urban/rural), household living conditions including household density, water supply, sewage and garbage collection, residency type and building material, and stratified by age groups, sex and race. The hierarchical models will be ordered according to the level that they act on the dependent variables (mental health hospitalizations and suicide). It is argued that mental health is conditioned by a series of proximal and intermediate factors, conditioned by socioeconomic situation, among which level of education, marital status, race, home conditions, region, and place of urban/rural residence, all considered social drivers.

To evaluate the impact of the countrywide cash transfer program on those outcomes, we will run Regression Discontinuity Design (RDD), Propensity Score Matching (PSM), and difference-in-differences, which are robust methods of impact evaluation in public health. This should help to identify the best statistical techniques to evaluate the impact of BFP on mental health-related hospitalization and suicide. Different evaluation methods make different assumptions. For instance, PSM assumes that after matching for the observed characteristics, there is no unmeasured confounding for the association between the intervention and the outcome. RDD instead assumes that people just below and just above the threshold of a continuous variable used as eligibility criteria for the intervention are “similar” in all relevant respects. Therefore, the difference in the outcome between the intervention groups is practically random near the threshold. PSM is a method that has been used in large electronic health records [10, 32]. It allows for matching where a true case-control design was not possible, which is usually the case for electronic health records of the type we will use in this project. A propensity score is a scalar summary of measured characteristics prior to treatment (potential confounders). Therefore, treated, and untreated subjects with equivalent propensity scores, also present similar pre-treatment characteristics. This method permits the generation of a grouping between intervention and no intervention that mimics the state of randomization. In our study, people who were part of one of the aforementioned programs would have specific characteristics, to control for that we will find a match for them on the remaining dataset (114 million) considering their age, sex, educational level, income, location of residence (urban/rural), household living conditions including household density, water supply, sewage and garbage collection, previous psychiatric hospitalization, residency type and building material. This allows us to inspect whether these subjects are at a higher or lesser risk of developing mental illness later in their lives. We assume that if the PSM models’ findings are similar to RDD, the results are robust given the underlying assumptions of each different model.

**Aim 2: To test four mechanisms and pathways of the social-economic intervention on reducing mental illness among youth; and Aim 3: To evaluate whether equity was a moderator of the effectiveness of the cash transfer program**, **e.g., whether the Brazilian cash transfer program improved the lives of most vulnerable subgroups (with lower income, black population, and women) compared to less vulnerable groups reducing mental health disparities.**

We will evaluate whether BFP program affects youth mental health through improving social drivers by running Regression Discontinuity Design (RDD) and Propensity Score Matching (PSM), and Structural Equation Modelling (SEM) for each of them and the outcomes. Such strategies allow us to examine the pathways by testing the impact of the intervention on variables that might be on the pathway of the relation between BFP and mental health outcomes. We hypothesize that BFP has an effect on reducing mental health-related hospitalizations and suicide among youth because it also affects their social drivers. Stratified analyses by municipality size, regions, states, and levels of Human Development Index (HDI) will also be performed.

We will include a set of covariates recognized as social drivers of mental illness for youth at the individual level such as income, income instability, unemployment, isolation and at the contextual level, variables from the municipalities where the youth live, such as population, fertility, mortality, migration, housing characteristics, characteristics of the neighbourhood, municipal income, labour, economic inequality (Gini index), Human Development Index (HDI), proportion of poor people and municipal coverage of the community mental health center and number of mental health professionals in the same municipality. We will also evaluate whether equity was a moderator of the effectiveness of the cash transfer program, e.g., whether the Brazilian cash transfer program improved the lives of most vulnerable subgroups compared to less vulnerable groups, thereby reducing mental health disparities. Therefore, we will repeat the analysis stratifying by subgroups with diverse ranges of income level, black compared with the white population, and female compared to male.

We will apply methods from the SEM group, to specify and test the paths laid out in Fig 1. SEM will be used to fit models to the specifications in Fig 1 to allow a judgement on which models best fit our data, therefore allowing the identification of the model, which might be the closest to the causal paths underlying the relationship between exposure and outcome, including potential confounders. Estimation is performed either by Maximum Likelihood. Besides identification of the best fitting models, SEM allows detailing the relationship between indicators (variables) included in the models. After deciding which models are optimal, the particular coefficient estimates are calculated, which can be of fundamental importance to the identification of the intermediate nodes that have the highest influence on the outcome, or which act as mediators or moderators. Mediators are useful representations of confounders, and as long as the path coefficients are calculated, one can precisely estimate the effects resulting from the mediator.

Aim 4: Investigate early life exposures, intergenerational aspects, and to forecast scenarios in Brazil until 2030 using microsimulation models.

Finally, to match this aim we will examine: timing of the intervention in the life course, e.g., if cash transfer delivered earlier in life (e.g., in 2004 when an adolescent was 14 years old) will be associated with lower mental health-related hospitalizations and lower suicide rates 10 years later (when the same adolescent will be 24 years old); and whether mental health-related problems such as suicidality, post-traumatic stress disorder (PTSD), violent behavior passes over to second generations; and, furthermore to forecast scenarios of mental health-related hospitalizations and suicide rates using microsimulation models. This will leverage the results from previous objectives and compare the impact of different BFP implementations on mental health-related hospitalizations and suicide in Brazil until 2030.

To answer the above sub-objectives, we propose the use of modeling for longitudinal data, since the events are observed over time. For sub-objective firstly we will apply extended Cox model [33], known as a marginal model for multiple or recurring events, to estimate whether the number of hospitalizations related to mental health increases or decreases in the course of life given whether the individuals received the intervention or not [34]. Secondly, we will run logistic regression models for longitudinal data [35] considering the age variable as a temporal measure, in which the outcome will correspond to a new binary variable in relation to having reduced or not hospitalization related to mental health (Yes/No). Regarding the intergenerational effect (sub-objective 2) on mental health issues, we will verify the influence of the parent’s mental health status on the child’s mental health through usual regression models, in which the outcome corresponds to the child’s mental health variable. Besides, we must consider a possible dependency between individuals in the same family. In this case, we will apply mixed models [36] to address the possible intra-individual correlation. All approaches will be validated using appropriate diagnostic and testing techniques.

The third stage of modelling will integrate the datasets and analyses above with Microsimulation Models (MS). Microsimulation is increasingly used in epidemiology and is useful to evaluate both overall and subgroup impacts of public policies [37] This is because microsimulation allows modelling of individual-specific characteristics and associated probabilities of outcomes, and when both are derived and retain the information of an existing retrospective dataset, the original correlation structure between variables and non-linear effects can be taken into account [37]. The MS integration is useful in our case, as both the heterogeneity and dynamic interactions of the population are relevant for the outcome under study. One co-investigator has developed microsimulation studies on the effect of economic crisis and BFP implementation scenarios in Brazil [38, 39] loping a platform for integration of these retrospective data and evaluations with microsimulation models for several health-related outcomes for the 100 Million Brazilian Cohort. A representation of the proposed MS model is presented in Fig 3. For the construction of this MS model, we will adopt a 2-step approach:

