#### Data and measures

Datasets, variables, and sample sizes.

***100 Million Brazilian Cohort*.** We will analyze a cohort of subjects registered in Unified Registry for Social Programs (CadÚnico). The CadÚnico is a data collection and storage system that contains individual records with demographic and socioeconomic information on the poorer half of the Brazilian population (n = 114,007,705). Anyone who meets the eligibility criteria can be registered by visiting one of the Centers for Social Assistance (CRAS) or be registered at home, as social workers visit households periodically to identify and register eligible individuals. The criteria to be eligible for CadÚnico registration are: having a monthly family income per capita of half the minimum salary in Brazil (778 reals in 2015) or less; or having a total family income (monthly) of up to three minimum salaries. The CadÚnico contains information about housing conditions, income and demographic characteristics of all the members of a registered family [26].

***Bolsa Familia Program (BFP)*.** The Brazilian Cash Transfer Program (BFP) is the largest poverty alleviation program in the world, with about 46 million people having received the benefit up to 2015. It has three aims: income supplement guarantee for immediate relief of extreme poverty (people who live with up to 70 reals per capita) [27]; access to public services (improving education, health, and citizenship of families); and productive inclusion to increase the capacity and job opportunities, and income generation among the poorest families [28].

In 2014, the eligibility criteria for participation in the program (which is more stringent than the conditions for eligibility to register in CadÚnico) was having an income of less than 77 reals (14 USD) monthly per person or less than 154 reals in cases where there is a child, adolescent or pregnant woman in the family. The benefits were: “basic benefit”, 77 reals monthly, regardless of family composition; an extra 35 reals to families with a child or adolescent between 0–15 years, or a pregnant or nursing woman; and an extra 42 reals per adolescent from 16–17 years, in 2014. Families living in extreme poverty can accumulate all these “basic benefits” to a maximum of 1,332 reals per month (235 USD).

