**Fig 2 pone.0272481.g002:**
[figure not shown]
Flowchart of non-beneficiary (non-BFP) and beneficiary of the Bolsa Familia Program (BFP) to test the association between BFP and youth mental health-related hospitalizations and suicide.

**Table 1 pone.0272481.t001:** Summary of the dataset’s description, from 2001 to 2018.

Dataset	Description	Sample	Variables of interest
The 100 Million Brazilian Cohort Baseline^70,73^	It was built from socioeconomic and demographic information of individuals applying for social benefits in Cadastro Unico (CadÚnico). CadÚnico is an extensive questionnaire with information on the household and on each individual.	114 million Brazilian cohort, including 66,079,181 Bolsa Familia Program beneficiaries and 47,928,524 non-beneficiaries. Among them 41,764,126, youth aged from 5–24 years old in the day of registration.	Demographic and socioeconomic variables (sex, age, ethnicity, education, work), conditions of the household (type of residence, material of household, household density, household supply, garbage destination etc), Health Care utilization, Institutional and community support (participation in groups, access to Social Assistance Reference Center, etc.) and Brazilian government social protection programs (BFP, etc).
Mortality Information System (SIM)^74,75,72^	The national system aimed to collect information on all deaths in Brazil death certificates. All deaths are recorded using a national standardized form and causes of death are registered according to the updated International Classification of Diseases CID-10.	All mortality cause (n = 21,313,290), including suicide (n = 181,527).	Demographic and socioeconomic variables (sex, age, ethnicity, education, work), place the death took place and primary and secondaries causes of death.
Hospital Information System (SIHSUS)^1^	All hospitalizations admissions financed by the Brazilian National Health System are recorded in this system. It includes about 80% of the Brazilian populations, approximately 150 million people	Hospitalizations from mental illness 5,478,980, including: 1,698,663 from alcohol and substance use-related disorders; 1,952,605 from schizophrenia; 832,974 due mood disorders, etc.	Identification and qualification of the patient, procedures, examinations, and medical acts performed, diagnosis, reasons for discharge, amounts due etc.

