Some limitations must be considered. The use of proxy in one of the four mechanisms proposed, physical injuries for impulsivity, can be a possible limitation in the analysis of mechanisms. However, assessment of impulsiveness and aggression in studies of risk factors for suicidal behavior, often depend on information from proxy informants, have been evaluated as robust [42]. Since both will be controlled by health care access, it is unlikely to have major differences between the group exposed and non-exposed. Quality of administrative data could also be challenging in these studies. Problems with quality can be related to problems with data collection and completeness of the data. However, most of the variables chosen for this project have less than 1% missing data. Most data that will be used for this proposal comes from CadÚnico that tend to be filled with precision due to the legal consequences on the beneficiaries. The forms are filled by trained interviewers, and missing information could result in not participating in the cash transfer program.

The large-scale data set will allow us to investigate comprehensively and in subpopulations the effects of BFP on youth mental health, as well test mechanisms of this effect. The use of these databases will allow exploring mental health outcomes with a high level of statistical power. The databases used in this study have national coverage, low under-registration, and some have already documented reliability. Therefore, this study will provide a comprehensive and representative analysis of the poor and extremely poor Brazilian population and reinforce the adequacy of these bases for epidemiological investigations. Results from this innovative project are expected to inform national efforts to prevent mental illnesses among youth from low-income communities in Brazil through the scale-up of economic interventions; our findings may also be relevant to other comparable middle income countries experiencing challenges, such as those resulting from the economic consequences of the COVID-19 pandemic, to address the burden of mental health problems among youth and reducing mental health disparities.

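### Agreement between PSM and RDD is taken to show robust results, but both rest on the same interview-recorded family income, so a shared reporting error near the eligibility line would not be revealed

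*Protocol article*

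**What the plan says.** The Analytic strategy section (Aim 1) lists RDD, PSM and difference-in-differences for the impact of BFP. It explains RDD as resting on the similarity of people on either side of "the threshold of a continuous variable used as eligibility criteria for the intervention", and draws from this: "Therefore, the difference in the outcome between the intervention groups is practically random near the threshold". It does not name the running variable. The paragraph ends with a rule: if PSM findings resemble those from RDD, the results are taken to be robust given each model's assumptions. Income is among the PSM matching variables listed there.

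The Data and measures section gives only one kind of continuous BFP criterion, per-capita family income. The 2014 rule is "having an income of less than 77 reals (14 USD) monthly per person or less than 154 reals", the higher figure applying where the family includes a child, an adolescent or a pregnant woman. Extreme poverty is described separately as "people who live with up to 70 reals per capita".

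On how income is recorded, Table 1 describes the cohort as built from applicants for social benefits and says "CadÚnico is an extensive questionnaire with information on the household and on each individual". According to Data and measures, eligible people "can be registered by visiting one of the Centers for Social Assistance (CRAS) or be registered at home". The limitations in the Discussion say that CadÚnico forms tend to be precise because of legal consequences for beneficiaries, and add: "The forms are filled by trained interviewers, and missing information could result in not participating in the cash transfer program".

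**The concern.** RDD has a causal reading only if families cannot precisely control which side of the line they are recorded on. Here the applicant supplies the figure that helps decide eligibility, and the protocol describes no check of that figure against another source. A family whose true income lies just above the line has a reason to report an amount just below it. If families who do so differ in underlying risk from those who do not, the jump at the line mixes the BFP effect with that difference.

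This matters most for the agreement rule. Two methods corroborate each other only against errors they do not share, and PSM and RDD both use recorded income. The result carries forward: RDD and PSM are reused for the mechanisms in Aims 2 and 3, and the retrospective effect estimates feed the 2019–2030 microsimulation (Aim 4, Step 2).

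**Working it through.** The protocol gives no sample size, bandwidth or expected effect for the RDD, so there is no stated figure to reproduce. The check is a reading of the text plus a short algebraic illustration.

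**Inputs from the protocol.** The income lines are 70, 77 and 154 reals, with 77 and 154 dated 2014. Income is recorded at interview from benefit applicants. Income is a PSM matching variable. The robustness rule names PSM and RDD.

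**Inputs assumed.** Let s be the share of families recorded just below the line who would report below it wherever they truly stood (sorters). Let r be their baseline risk relative to other families. The protocol supports no value for either. The true BFP effect is set to nil.

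**RDD.** Families just above the line contain no sorters, so their relative risk is 1. Families just below have average relative risk (1 − s) + s·r. Hence

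apparent risk ratio (below/above) = 1 + s(r − 1).

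If the true density of families is the same on both sides, and a share m of all families near the line are sorters, then s = 2m/(1 + m). The recorded density ratio (below/above) is (1 + m)/(1 − m) = 1/(1 − s).

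| s | r = 0.5 | r = 2 | density ratio |
|---|---|---|---|
| 0% | 1.00 | 1.00 | 1.00 |
| 10% | 1 − 0.10 × 0.5 = 0.95 | 1 + 0.10 × 1 = 1.10 | 1/0.90 = 1.11 |
| 20% | 1 − 0.20 × 0.5 = 0.90 | 1 + 0.20 × 1 = 1.20 | 1/0.80 = 1.25 |

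In terms of m, with r from 0.7 to 1.5: m = 10% gives (0.9 + 0.2 × 0.7)/1.1 = 0.95 to (0.9 + 0.2 × 1.5)/1.1 = 1.09, with density ratio 1.1/0.9 = 1.22.

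No sample size enters the formula, so more data leave the bias where it is.

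**PSM.** Suppose sorters form a share p1 of matched beneficiaries and p0 of matched non-beneficiaries. Under a nil effect,

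apparent risk ratio = [1 + p1(r − 1)] / [1 + p0(r − 1)].

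Sorting to obtain the benefit would make p1 larger than p0. The ratio is then below 1 when r < 1 and above 1 when r > 1, the same side of 1 as the RDD ratio. Matching on recorded income does not undo this, because recorded income is the quantity in error.

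**Reading the rule against this.** With sorting and a nil effect, PSM and RDD can both show benefit, or both show harm. The agreement rule would call either result robust.

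**The case against.** The strongest reply is that the sentence on randomness is conditional. It follows a statement of what RDD assumes, and the agreement rule is itself worded as an assumption. That stands: the article does not claim to have verified similarity at the BFP threshold.

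Density tests and donut analyses are also routine detail that a journal article may leave to an analysis plan. That stands too, so their absence is not the point. What remains is a stated rule for judging robustness that cannot do its job if the two methods share an error.

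The Discussion offers legal consequences and trained interviewers as reasons for precise forms. These may reduce under-reporting. The argument concerns data quality and completeness, however, and does not exclude income reported just under the line. Difference-in-differences is also planned, but the agreement rule does not refer to it.

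A reader might infer several stronger things that the documents do not support:

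- **That families did sort, so the RDD is invalid.** Nothing shows that they did. Income as the running variable is itself an inference, though a strong one.
- **That the incentive is overwhelming.** A one-person family at 77 reals would gain 77/77 = 100% from the basic benefit, but a family of four at that level has 4 × 77 = 308 reals and gains 77/308 = 25%.
- **That a false effect would come with a very narrow interval.** RDD uses families near the line, and no count or bandwidth is given.
- **That reported incomes heap on round values.** The documents do not say so.

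**Conclusion.** The point holds as a weakness in a stated inference rule, not as evidence of bias. Agreement of PSM with RDD does not establish robustness when both depend on income recorded from benefit applicants, because misreporting near the line could move both estimates the same way. The size and direction are unknown. The range 0.95 to 1.10 illustrates 10% sorters with 0.5 to 2 times the risk of others, under a nil true effect and no sorters above the line; neither the 10% nor the risk ratios come from the protocol. The conclusion also assumes that per-capita family income is the running variable. The change is worth making because it bears on the study's main causal claim and can be done with data already held.

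**What to change.** In the Aim 1 text of the Analytic strategy section:

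1. Name the running variable and list the cut-offs used, by calendar year and family type, since the text gives 70, 77 and 154 reals.
2. State the absence of precise manipulation of recorded income as an assumption. Say that it is assignment near the line, not the outcome difference, that is treated as close to random.
3. Before outcomes are analysed, check at each cut-off the density of recorded income, allowing for any heaping, and the continuity of pre-registration covariates such as previous psychiatric hospitalization and housing. Both covariates are already in the PSM matching list.
4. Add a donut RDD, leaving out families closest to the line, as a sensitivity analysis.
5. Replace the agreement rule with, for example: *RDD will be taken to support PSM only at cut-offs without evidence of sorting; elsewhere, agreement between them will be reported as descriptive.*

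The cost is a few added analyses and a short rewording. The donut estimate will have a wider interval, by an amount that the documents do not allow to be computed.

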Preventing mental illness earlier during development could decrease subsequent mental health-related hospitalizations and suicide attempts. However, prevention poses a tough challenge, as these outcomes are usually the final stage of a series of small breakdowns that happen at several levels in the life course. Considering the multi-causality of the phenomenon, it is important to investigate several social drivers, risks, and protective factors at the individual and contextual level. Poverty, gender and racial inequality are associated with increased mental illness [6] and suicide [7, 8]. This might be explained by increased stress, family difficulties, alcoholism, impulsivity, violence and parental mental illnesses among the poor [3, 9–11]. However, those mechanisms are yet to be fully understood and tested, especially among youth in a LMIC setting.

Brazil has one of the largest mental health-related hospitalizations among youth, and suicide is the third most common reason for death due to external causes, and alarmingly both have increased over the last 13 years. The World Health Organisation (WHO) recommends that suicide prevention should be prioritized on the global public health agenda [12]. However, it remains unclear what interventions are best suited for targeting youth at a population level and what preventive interventions delivered earlier in life have a long-term effect on preventing mental health-related hospitalizations and suicide.

The Brazilian government introduced the Bolsa Familia Programme (BFP) in 2003 [13] to promote social inclusion and strengthen human capital among the poorest. Poverty alleviation programs could influence mental illness by diverse pathways [3, 5, 9] through decreasing income inequalities or by reducing socioeconomic hardship through increased family income, which might result in stress reduction, less family disruption, or decreased alcohol consumption [14]. Therefore, we might expect government poverty alleviation programs such as BFP to have an impact. However, whether this Brazilian government program has impacted, and knowledge of the pathways and mechanism of its impact, on youth mental illness and suicide remains unknown.

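### The Aim 1 propensity-score matching list omits registration year, area, family composition and race, so the matched BFP effect risks residual confounding by variables the study largely holds

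*Protocol article*

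**What the plan says.** The Analytic strategy, Aim 1, names three impact designs: regression discontinuity (RDD), propensity score matching (PSM) and difference-in-differences. For PSM it says that each beneficiary will be matched within the 114 million cohort "considering their age, sex, educational level, income, location of residence (urban/rural), household living conditions including household density, water supply, sewage and garbage collection", and the list then ends with "previous psychiatric hospitalization, residency type and building material". The same paragraph states what the method needs: "PSM assumes that after matching for the observed characteristics, there is no unmeasured confounding for the association between the intervention and the outcome". Similar PSM and RDD findings will be taken as a sign of robustness.

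Other sections describe what determines receipt and outcomes. Data and measures gives the 2014 income limit as below 77 reals per person, "less than 154 reals in cases where there is a child, adolescent or pregnant woman in the family" being the alternative limit. Background says "Poverty, gender and racial inequality are associated with increased mental illness" and, of youth mental health hospitalizations and suicide, that "alarmingly both have increased over the last 13 years". Table 1 lists for the cohort baseline "Demographic and socioeconomic variables (sex, age, ethnicity, education, work), conditions of the household".

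**The concern.** A propensity score balances only what enters it. The Aim 1 list is printed as complete, whereas the covariate sets for the social-driver regressions and for Aims 2 and 3 are partly introduced as examples. Four factors that the protocol itself treats as relevant are absent: year of registration, state or municipality, family composition and race. The contrast within Aim 1 is telling. The associational regressions are stratified by race and adjusted for access to mental health care. The causal comparison, which needs more control of confounding, has neither.

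At stake is the credibility of one of three main estimates of the BFP effect. With 41,764,126 youth in the cohort, random error may be small, so even a modest imbalance could look statistically decisive. The retrospective effect estimates also feed the microsimulation to 2030.

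**Working it through.** **Step 1: the list.** It contains age, sex, education, income, urban/rural residence, household conditions (density, water, sewage, garbage), previous psychiatric hospitalization, residency type and building material. The nearest items to the missing factors are urban/rural (for area) and household density (for family composition). Both are partial proxies.

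**Step 2: the missing factors against the rest of the protocol.**

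| Factor | Link to BFP receipt | Link to outcomes | Held? |
|---|---|---|---|
| State or municipality | BFP coverage differs between municipalities (Study innovation) | Lower suicide where coverage is higher (Study innovation); region named as a driver (Aim 1); municipal factors listed (Aims 2–3) | Municipality code (Linkage); HDI and Gini (Table 1) |
| Family composition | Sets the 77 or 154 real limit; children's ages set benefit amounts (Data and measures) | Named as a driver (Aim 1) | Data on all family members (Data and measures) |
| Registration year | Inferred: BFP began in 2003, inside the 2001–2018 window | Inferred: both outcomes rose over time (Background) | Age is defined at the day of registration (Table 1) |
| Race | None stated | Background; Aim 1 drivers | Ethnicity (Table 1) |

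Without registration year, a 14-year-old registered in 2004 can be matched to one registered in 2014, with different background rates and follow-up time.

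**Step 3: whom the eligibility split affects.** Youth are aged 5–24 at registration (Table 1). Under the 2014 rule, family composition decides eligibility only between 77 and 154 reals per person. The benefit rules count adolescents up to 17, so the family of anyone aged 5–17 already meets the composition condition. Because age is in the score, the split separates beneficiaries from controls mainly at ages 18–24 in that income band. For younger youth, composition matters through benefit amount and as an outcome driver.

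**Step 4: size.** The protocol gives no effect size, trend or imbalance, so there is no figure of its own to reproduce. The cohort counts do agree: 66,079,181 + 47,928,524 = 114,007,705, so the beneficiary share is 66,079,181 / 114,007,705 = 0.5796.

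The following is an illustration on assumed inputs. For one omitted binary factor with outcome rate ratio RR and prevalence p1 in beneficiaries and p0 in matched controls, the spurious rate ratio under a true null is

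bias = (1 + p1(RR − 1)) / (1 + p0(RR − 1)).

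With p0 = 0.50:
- RR 1.2, p1 0.55: 1.11 / 1.10 = 1.009
- RR 1.5, p1 0.60: 1.30 / 1.25 = 1.040
- RR 2.0, p1 0.70: 1.70 / 1.50 = 1.133

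The chance that this bias alone reaches two-sided 0.05 with d events is about Φ(|ln bias| × √(d × 0.5796 × 0.4204) − 1.96). For d = 20,000 the root is √4,873 = 69.8. For bias 1.040, 0.0392 × 69.8 = 2.74, and Φ(0.78) = 0.78.

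| Events (assumed) | Bias 1.009 | Bias 1.040 | Bias 1.133 |
|---|---|---|---|
| 5,000 | 5% | 28% | 99% |
| 20,000 | 9% | 78% | nearly 100% |
| 50,000 | 17% | 99% | nearly 100% |

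The 58:42 split is for all ages before matching. One-to-one matching would replace 0.5796 × 0.4204 = 0.2437 by 0.25, which changes little.

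**The case against.** **This is a condensed article, and the final propensity model may be set elsewhere.** That would excuse silence, but the article states a specific list. The point concerns that list as printed.

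**Aims 2 and 3 already cover part of the gap.** They use PSM for outcomes as well as mediators, plan municipal covariates, stratify by region, state and HDI, and repeat the analysis by race, which holds race fixed within each stratum. This stands, and it confines the point to the Aim 1 matched effect, since that text does not extend the Aim 1 list.

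**Race is not shown to be a confounder.** This also stands. The protocol reports an association with the outcomes and nothing on receipt.

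**The 77/154 split mostly disappears once age is matched.** Largely right, as Step 3 shows. A reader might infer that beneficiary families with children are set against childless families throughout the cohort. The documents support that mainly for ages 18–24, and household density gives partial control.

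**PSM is not the only design.** RDD does not depend on this list, difference-in-differences removes fixed differences, and the microsimulation draws on the retrospective estimates in general. This limits the damage. It does not repair the matching, and agreement with RDD, which is informative near the threshold, does not show that the matching set is adequate.

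**Conclusion.** The point holds for the Aim 1 PSM. Its list leaves out measured variables that the protocol links to receipt and outcomes: area and family composition directly, calendar time by inference. Race is linked to the outcomes only. The supported conclusion is a risk of residual confounding, not a demonstrated bias.

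Neither direction nor size can be computed from the document. The 1.009 to 1.133 range and the percentages rest wholly on assumed prevalences, rate ratios and event counts. A reader might go further and assume outcomes rising 2–5% a year and a 2–4 year gap in registration between matched groups, giving 1.02² = 1.04 to 1.05⁴ = 1.22, and call that as large as the BFP effect. The documents do not support this: they give no slope, do not say that the groups differ in registration year, and state no expected effect.

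**What to change.** Extend the Aim 1 matching list to include:
- registration year and state, by exact matching or in the score;
- baseline municipal characteristics already held, such as HDI and Gini;
- number and ages of children and adolescents in the family;
- race/ethnicity.

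Report covariate balance and propensity overlap after matching. If the Aims 2 and 3 covariates were always meant to apply to Aim 1, say so.

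Do not add income relative to the family's own BFP cut-off. That puts the eligibility rule into the score, brings receipt close to deterministic and threatens overlap. Pregnancy or nursing status and municipal mental health coverage are not named in Table 1, so confirm that they are held before relying on them.

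The change is to wording, made before analysis, using variables that the protocol shows as held. The downside is a somewhat smaller matched fraction, which the overlap report will make visible.
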